## Discussion

The goal of this study is to determine whether persistent balance and gait deficits following mTBI are attributable to improper central sensorimotor integration and to examine the potential for augmented rehabilitation to improve daily activity levels. In particular, this study is unique in its investigation of central sensorimotor integration in people with persistent balance complaints following mTBI in that confounding covariates such as vestibular disruption, neurocognition, and physical activity will be objectively quantified. Additionally, if we find that the quantitative balance, gait, or novel CSMI measures have a significantly greater AUC compared to the clinical measures (BESS, gait speed, SOT) at detecting patients with chronic mTBI, this will indicate the necessity for objective quantification of gait and balance deficits for mTBI assessment.

If a portion of subjects with chronic balance problems after mTBI have abnormal CSMI test measures but normal clinical vestibular testing results, this suggests that sensory integration processes in the brain can be impaired following mTBI, even without peripheral sensory deficits, and that abnormal central sensorimotor integration plays a key role in persistent abnormal balance in subjects with normal vestibular function. If a portion of mTBI subjects have abnormal CSMI test measures and abnormal clinical vestibular function, the key mediator for balance problems is less clear and may be due to the peripheral vestibular dysfunction, abnormal central sensorimotor integration, or inadequate adaptation of central sensorimotor integration to account for abnormal sensory information. If we find that abnormal central sensorimotor integration mediates abnormal static or dynamic balance, rehabilitation will need to be focused on improving central sensorimotor integration to improve balance. If we find that CSMI scores improve with rehabilitation, we will conclude that central sensorimotor integration strategies are flexible and can improve with training. Further, if we find that central sensorimotor integration and gait and balance jointly improve with rehabilitation, we will have further evidence that central sensorimotor integration plays a key role in the mediation of gait and balance following mTBI. If we find a greater improvement in the ABF group, we will conclude that ABF may facilitate improved rehabilitation. Finally, if we find that people with central sensorimotor integration impairment maintain improvements after stopping the use of ABF device, we will conclude that a recalibration of sensory integration and/or sensorimotor transformation for balance has occurred, rather than sensory substitution that requires active ABF. If we find that sensory strategies can change with practice and biofeedback, we will conclude that this targeted approach to balance rehabilitation should be explored further in a larger, randomized trial. It is possible that different subclasses based on CSMI measures respond differently to rehabilitation or ABF-augmented rehabilitation. In such a case, the results of this study will provide valuable information for powering an in-depth future study carefully examining the relationship between CSMI subclasses and the response to rehabilitation with and without ABF. The results of this study will further our understanding of the mechanisms underlying posture and gait dysfunction in individuals with chronic mTBI and inform future studies about the efficacy of ABF augmented rehabilitation programs.

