### Participants

The study will include 65 mTBI participants and 65 control subjects for the cross-sectional arm of the study. All subjects will be between the ages of 18 and 60. Participants in the mTBI group will have a diagnosed mTBI or concussion and chronic, non-resolving complaints of balance problems determined by a score >0 on the Dizziness Handicap Inventory (DHI) at the time of testing and > 3 months post-injury. Control subjects will be gender and age matched to the mTBI group. For the second arm of the study, a subset of 40 mTBI subjects with abnormal central sensorimotor integration with or without peripheral vestibular or ocular motor deficits will be randomized into two rehabilitation groups, experimental treatment and standard of care, consisting of two rehabilitation sessions per week for 6 weeks. All subjects will be tested at either Oregon Health & Science University or the VA Portland Health Care System. All rehabilitation will take place at Oregon Health & Science University. Informed written consent will be obtained from all participants.

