### Inclusion and exclusion criteria

Inclusion criteria for mTBI recruitment are 1) a diagnosis of mTBI based upon VHA/DoD criteria with persisting symptoms >3 months post injury [44], 2) between 21–50 years old, 3) a score >0 on the DHI, 4) minimal cognitive impairment; a score between 0 and 8 on the Short Blessed test for cognitive function [45], and 5) may or may not have had a loss of consciousness (LOC) with their initial injury. Inclusion criteria for controls are between 21–50 years old and no history of mTBI or brain injury. Exclusion criteria are: 1) have had or currently have any other injury, medical, substance or neurological illness that could potentially explain balance deficits (e.g., CNS disease, stroke, moderate TBI, lower extremity amputation) 2) meet criteria for moderate to severe substance use disorder within the past month, as defined by DSM-V, 3) display behavior that would significantly interfere with validity of data collection or safety during study, 4) be in significant pain during the evaluation (5/10 by patient subjective report), 5) be a pregnant female (balance considerations), 6) have past history of peripheral vestibular pathology or ocular motor deficits, 7) have significant hearing loss that would interfere with Study 1 no worse than 60 dB HL (PTA 0.5–3 kHz) and Study 2; hearing loss no worse than 30 dB HL (PTA 0.5–3 kHz), in better ear, with the difference in ears being less than 15 dB PTA, or 8) be unable to abstain for 24 h in advance of testing in the use medications that might impair their balance.

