#### Statistical analysis

To determine if objective/novel measures of balance will better distinguish people with mTBI from control subjects than clinical measures, we will use logistic regression classification models. Improvements in classification will be determined by calculating the area under the curve (AUC) of the receiver-operator characteristic and then comparing AUC for each traditional clinical measure with the novel objective measures. Significance will be assessed using bootstrapping to determine if the observed differences in AUC are greater than would be expected by chance at a level of 0.05.

To determine if a subset of people with mTBI will have abnormal CSMI test measures, even without peripheral vestibular or ocular motor deficits, we will use descriptive statistics to characterize the distribution of CSMI test measures and vestibular/ocular motor scores. We will define CSMI test measures and vestibular/ocular motor scores as abnormal if the scores are greater than 2 standard deviations from the mean in controls. We will then classify mTBI subjects into one of 4 CSMI-vestibular/ocular motor categories 1) abnormal CSMI –abnormal vestibular/ocular motor scores, 2) abnormal CSMI –normal vestibular/ocular motor scores, 3) normal CSMI –abnormal vestibular/ocular motor scores, 4) normal CSMI –normal vestibular/ocular motor scores.

To determine if the observed relationship between poorer static/dynamic balance performance and mTBI is regulated/mediated by central sensorimotor integration, we will use mediation analysis. Mediation analysis [49] will allow for the partitioning of the association between mTBI and chronic imbalance into two parts, the direct relationship of mTBI on balance impairment as well as the causally mediated effect of mTBI on central sensorimotor integration, which, in turn is having the actual effect on imbalance. These varying generative mechanisms of balance deficits will be assessed by utilizing linear models relating mTBI to CSMI test measures alongside models of mTBI and CSMI test measures jointly affecting imbalance using the apportionment methods described by Baron and Kenny [49].

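### A greater AUC for objective measures can show better separation of the two enrolled groups, not the necessity of objective testing for mTBI assessment that the Discussion announces in advance

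*Protocol article*

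**What the plan says.** Hypothesis (a) of Study 1, in the Background, is that objective measures distinguish people with mTBI from controls better than clinical measures do.

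The Study 1 Statistical analysis section tests this with logistic classification models, "comparing AUC for each traditional clinical measure with the novel objective measures". Bootstrapping is used to judge whether a difference is "greater than would be expected by chance at a level of 0.05".

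The groups are fixed in two places:
- Participants: "The study will include 65 mTBI participants and 65 control subjects for the cross-sectional arm of the study". The mTBI group has "chronic, non-resolving complaints of balance problems determined by a score >0 on the Dizziness Handicap Inventory (DHI) at the time of testing" and is more than 3 months post-injury.
- Inclusion and exclusion criteria: controls have no history of mTBI or brain injury. The exclusion list, which is not restricted to either group, removes people with "any other injury, medical, substance or neurological illness that could potentially explain balance deficits".

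The Discussion then sets the condition, "if we find that the quantitative balance, gait, or novel CSMI measures have a significantly greater AUC compared to the clinical measures (BESS, gait speed," with SOT as the third measure, and the conclusion drawn from it: "this will indicate the necessity for objective quantification of gait and balance deficits for mTBI assessment".

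**The concern.** The planned test asks whether one measure separates two groups better than another. The announced conclusion is that a class of measurement is needed. Two things are missing between them.

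- **Comparison.** Someone assessing a patient can use BESS, gait speed and SOT together. Objective testing is needed only if that set falls short and the objective measure makes up the shortfall. Comparing AUCs one measure at a time does not address this.
- **Sample.** The cases enter with an mTBI diagnosis and a positive symptom questionnaire; the controls are healthy. People with imbalance from other causes, and people with mTBI but no complaints, are outside the sample. The conclusion nevertheless ends on mTBI assessment without restriction.

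At stake is what the trial may claim from a positive Study 1 result. A correct finding of better discrimination would be reported as evidence that instrumented testing is indispensable.

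**Working it through.** The article gives no AUC, AUC difference or power for this comparison, so there is no stated figure to reproduce. The 65 per group rests on the coefficient of variation of Kp in a reference group. All AUCs and correlations below are assumptions.

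**1. Superiority over single measures versus added value**

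Model: three clinical measures, normal with equal variances, equal AUC and within-group correlation ρ.
- Shift of one measure: d = √2 · z(AUC).
- Joint separation: D² = 3d² / (1 + 2ρ). Joint AUC = Φ(D/√2).

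AUC 0.65 gives d = 0.545; AUC 0.70 gives d = 0.742.

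| Single AUC | ρ | D | Joint AUC |
|---|---|---|---|
| 0.65 | 0.2 | 0.798 | 0.714 |
| 0.65 | 0.3 | 0.746 | 0.701 |
| 0.70 | 0.2 | 1.086 | 0.779 |
| 0.70 | 0.3 | 1.016 | 0.764 |

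Now take an objective measure that only reflects the best clinical composite, with correlation r and otherwise noise. Its AUC is Φ(rD/√2). For single AUCs of 0.65:
- r = 0.85, ρ = 0.3: Φ(0.85 × 0.746/√2) = 0.673
- r = 0.95, ρ = 0.2: Φ(0.95 × 0.798/√2) = 0.704

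The measure exceeds each clinical measure (0.65) yet by construction adds nothing to the three together.

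**2. What significance would require at 65/65**

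The Hanley-McNeil standard error at AUC 0.70 is 0.046. With a correlation c between the two AUC estimates, the smallest significant difference is 1.96 · √(2 · 0.046² · (1 − c)): about 0.13 for c = 0 and 0.09 for c = 0.5. The gaps in step 1 are 0.673 − 0.65 = 0.023 to 0.704 − 0.65 = 0.054, so most such studies would not reach significance against a given comparator.

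A simulation of the 0.65 scenario (65 per group, DeLong variance, z > 1.96, 3,000 runs per setting) gives:
- significantly better than all three clinical measures: under 1% of studies;
- significantly better than at least one of the three: about 21% to 61%.

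The frequency thus depends on whether one or all comparators must be beaten, which the article does not fix.

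**3. Dependence on the comparator group**

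Suppose a marker has AUC 0.80 against healthy controls, and people with imbalance but no mTBI share a fraction f of its shift. Against that group the AUC is Φ(d(1 − f)/√2):

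| f | 0 | 0.25 | 0.50 | 0.75 | 1 |
|---|---|---|---|---|---|
| AUC | 0.80 | 0.74 | 0.66 | 0.58 | 0.50 |

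The Study 1 sample cannot say which column applies, because it contains no such people.

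**4. The contrast itself**

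Table 3 derives the SOT ratio scores from sway, and gait speed is a quantity. Doing better than these two does not show that objective quantification as such is required, since they are already quantified.

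**The case against.** The strongest reply is that the analysis matches its hypothesis. Hypothesis (a) asks which measures discriminate better, and an AUC comparison answers that. The sample is openly described, and excluding other causes of imbalance is reasonable in a mechanistic case-control study. An added-value model answers a question the article does not pose, and an unseen analysis plan may contain one. All of this stands: the AUC comparison should be kept, and the absence of a nested model is not in itself a fault. It does not rescue the Discussion sentence, which draws a conclusion the analysis was not built to give.

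Three stronger readings are tempting and are not supported:
- **One objective measure beating one clinical measure is enough.** The text lets any one of three objective families suffice, but it names the clinical comparators as a plural list. One-against-one is only the weakest reading allowed.
- **The condition ignores case selection.** The condition itself refers to chronic mTBI, and the sentence before it to persistent balance complaints. Only the closing words drop the limit, so the overreach is narrower than the final clause alone suggests.
- **A false claim is likely.** The illustration uses assumed population AUCs and an objective measure made to mirror the clinical composite. Nothing in the article says that CSMI or sensor measures behave so, and if all three comparators must be beaten the illustrated result would almost never be significant.

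**Conclusion.** The stated inference is wrong as written. A significantly greater AUC in this design supports hypothesis (a): better discrimination of chronic, balance-complaining mTBI from people with no mTBI and no other cause of imbalance. It does not show added value over BESS, gait speed and SOT jointly, and it does not extend to mTBI assessment in general. This holds whether one or all of the clinical comparators must be beaten, and it does not rest on the assumed AUCs, which only make the distinction concrete.

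Severity is minor to moderate. No endpoint, test or sample size is wrong, and a reader should not infer that the AUC analysis is invalid or that the article issues a clinical recommendation. It announces an interpretation that the data cannot carry.

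**What to change.** 1. Keep the AUC comparison as the test of hypothesis (a).
2. In the Discussion, drop the necessity wording and state that a greater AUC would indicate better discrimination of chronic, balance-complaining mTBI from healthy adults.
3. State whether one or all of BESS, gait speed and SOT must be exceeded for that conclusion.
4. If added value is to be claimed, fit one logistic model with BESS, gait speed and SOT together, add the objective measure, and report the likelihood-ratio test and the cross-validated AUC gain.
5. Leave any statement about mTBI assessment in general to a study with a comparator group suited to that question.

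Cost: a reworded sentence, a narrower conclusion and, if item 4 is taken up, one further analysis on data already collected.

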**Fig. 1 Fig1:**
[figure not shown]
Sensory systems contributing to static and dynamic balance

A proportion of individuals with mTBI who do not have prominent or measurable sensory deficits may still have balance problems attributable to abnormal central control of balance. Central sensorimotor integration is a critical aspect of balance control that may underlie dysfunction in static and dynamic balance. Proper central sensorimotor integration relies on the central nervous system to 1) select the optimal combination of sensory sources for balance and 2) reweight the sensory contributions as sensory conditions change [22, 23]. When peripheral vestibular, visual, and somatosensory systems are intact, difficulty performing static or dynamic balance tasks under challenging surface and/or visual conditions may be due to centrally-mediated suboptimal weighting and/or reweighting of vestibular, visual, and somatosensory information or due to abnormal sensory-to-motor transformations that inappropriately scale the magnitude of corrective motor actions [22–24]. For example, standing or walking on compliant foam or irregular surfaces requires the nervous system to rely more on vestibular and visual inputs while down-weighting the normal dependence on somatosensory information [22]. This reweighting is also important for individuals with sensory impairment, as altered patterns of weighting are necessary to compensate for the sensory dysfunction. Some patterns of compensation may be more functional than others, suggesting an important role of rehabilitation in helping subjects develop effective compensation strategies to improve recovery of central sensorimotor integration and balance [24]. However, central sensorimotor integration has not been systematically characterized in patients with mTBI, regardless of sensory loss.

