The heterogeneity of balance deficits and varied rates of recovery after mTBI suggest varied etiologies and a need for interventions that address the underlying causes of poor balance function. Over-simplified clinical balance measures often do not account for the complex integration of sensory and motor systems. Therefore, the first goal of this study is to characterize balance deficits in people with mTBI who have chronic, non-resolving balance deficits compared to healthy control subjects without a history of mTBI. We hypothesize that a) objective measures of central sensorimotor integration, static and dynamic balance will better distinguish people with mTBI from control subjects than clinical measures, b) a subset of people with mTBI will have abnormal central sensorimotor integration test measures, even without peripheral vestibular or ocular motor deficits, and c) the relationship between poorer static/dynamic balance performance and mTBI is regulated/mediated by central sensorimotor integration. The second goal is to determine if augmenting a traditional balance rehabilitation program with a wearable-sensor based ABF system improves central sensory integration in patients with chronic mTBI compared to the standard balance rehabilitation program. Our central hypothesis is that chronic balance deficits after mTBI result from impairments in central sensorimotor integration that may be helped by rehabilitation that challenges balance while simultaneously providing feedback on balance performance. We hypothesize that a) central sensorimotor integration scores will improve with rehabilitation and ABF will increase the improvement of central sensorimotor integration scores beyond the standard of care, b) intervention with ABF will improve objective measures of balance and c) people with central sensorimotor integration impairment will show sustained improvement in central sensorimotor integration scores and balance after rehabilitation with ABF.

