#### Clinical testing for classification and covariates

To classify mTBI participants as with or without vestibular dysfunction, standard vestibular testing will be performed as described in Table 4. Clinical tests to examine potential covariates of sensory loss will also be included at the initial visit in Study 1.

**Table 4 Tab4:** List of clinical sensory and vestibular tests for classification and covariates / comorbidities of primary and secondary outcomes

Domain Tested	Test	Description	Positive Result
Sensory	Proprioception test	Assess the ability of the participant to detect the position of the great toe or ankle as it is moved by a researcher / clinician	Unable to detect changes in position
	Visual Vertical Test	Requires participant to orient a line to vertical and quantifies the deviation from vertical	Falls outside control group mean ± 2 SD
Ocular Motor	Saccadic Latency	Assesses the ability to make a rapid eye movement, latency would be the time it takes to initiate a saccade (eye movement) after the target has moved	Falls outside control group mean ± 2 SD
	Gaze	Assesses the ability to maintain stable vision on a fixed target.	
	Smooth Pursuit	Assesses the ability to accurately track/follow a moving/sinusoidal target with the eyes.	
	Convergence	Assesses the ability to view a close target without double vision	
Vestibular	cVEMP	Neurophysiological test assessing the function of the saccule	Falls outside control group mean ± 2 SD
	oVEMP	Neurophysiological test assessing the function of the utricle	
	Caloric	Assesses function of the lateral semi-circular canals and superior branch of the vestibular nerves	
	Head Impulse	Assesses function of semi-circular canals and vestibular nerve branches, specifically the lateral canals/superior vestibular nerve	

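### The Discussion would infer central impairment without any peripheral sensory deficit, but the Study 1 classification checks only vestibular and ocular motor function

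*Protocol article*

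**What the plan says.** All references are to the protocol article.

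- **Hypothesis (Background, Study 1 hypothesis b).** A subset of people with mTBI will have abnormal CSMI measures "even without peripheral vestibular or ocular motor deficits".
- **Classification (Study 1, Statistical analysis).** "We will then classify mTBI subjects into one of 4 CSMI-vestibular/ocular motor categories". Scores count as "abnormal if the scores are greater than 2 standard deviations from the mean in controls". The cell that answers hypothesis b is "2) abnormal CSMI –normal vestibular/ocular motor scores".
- **Sensory tests (Clinical testing for classification and covariates, Table 4).** A proprioception test is also done: "Assess the ability of the participant to detect the position of the great toe or ankle" as it is moved. It is positive when changes in position are not detected. A visual vertical test is listed in the same sensory domain. The text describes the tests of sensory loss as potential covariates.
- **Interpretation (Discussion).** Abnormal CSMI with normal clinical vestibular results is to be read as follows: "this suggests that sensory integration processes in the brain can be impaired following mTBI, even without peripheral sensory deficits".

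**The concern.** The protocol describes what is absent in three ways, and they do not have the same scope. The hypothesis and the cell concern vestibular and ocular motor deficits. The condition stated in the Discussion names vestibular results alone. The conclusion covers peripheral sensory deficits in general, which includes the somatosensory system.

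The gap matters because the missing system feeds the outcome. A CSMI result may be abnormal because the proprioceptive weight is abnormal, and that weight may have shifted because proprioception itself is poor. With normal vestibular and ocular motor results, such a person falls in the cell read as evidence of central impairment. At stake is the interpretation of one of the three Study 1 hypotheses. The randomised comparison in Study 2 is not affected, because entry there depends on abnormal CSMI whatever the vestibular or ocular motor status.

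**Working it through.** The protocol gives no figure to reproduce, so the check sets the passages side by side. A short illustration of scale follows.

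**1. Scope of each statement**

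| Place | Systems required to be normal |
|---|---|
| Hypothesis b (Background) | peripheral vestibular, ocular motor |
| Second of the four cells (Study 1, Statistical analysis) | vestibular, ocular motor |
| Condition in the Discussion | vestibular |
| Conclusion in the Discussion | all peripheral sensory systems |

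The first two rows agree. The last row is wider than each of the others.

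**2. Does the untested system bear on CSMI?** Yes, on the protocol's own account. In the model description (text after Fig. 2), the proprioceptive weight is estimated in conditions 1 and 2, and the sensory weights are said to be affected by sensory abnormalities. The Background adds that people with sensory impairment need altered weighting to compensate. An abnormal weight can therefore accompany proprioceptive loss.

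**3. Does any stated rule act on the proprioception result?** None was found. The four-cell rule has no somatosensory axis, and the Study 1 mediation text does not mention it. The only stated role is that of a potential covariate. The four cells are a descriptive count with no model attached, so no covariate adjustment is stated for them.

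**4. Does eligibility close the gap?** Only in part. The first exclusion criterion removes people with another past or current injury or illness that could explain balance deficits. It does not say what happens to a deficit first found at baseline testing, and Table 4 defines a positive result.

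**5. Illustration of scale.** The input from the protocol is 65 mTBI participants. The prevalence p of a positive proprioception test is assumed.

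- Expected number = 65 × p
- Chance of at least one = 1 − (1 − p)^65

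| Assumed p | Expected number | Chance of at least one |
|---|---|---|
| 2% | 1.3 | 73% |
| 5% | 3.25 | 96% |
| 10% | 6.5 | 99.9% |

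These counts are for the whole cohort. They are a ceiling for the key cell, since not everyone with a positive test will have abnormal CSMI and normal vestibular/ocular motor results. The size of that cell is not given, so no share of it can be stated.

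**6. Visual vertical.** Table 4 calls this test positive outside the control mean ± 2 SD. For a normally distributed score, 2 × (1 − Φ(2)) = 4.55% of unaffected people fall outside, and 65 × 0.0455 ≈ 3. The protocol does not say which sensory system the test isolates. Making it a condition of the key cell would remove some unaffected people for an unclear gain.

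**The case against.** Much of the case on the other side stands, and it limits the point.

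- **The classification fits its hypothesis.** A reader might infer that the four cells are mis-specified. They are not: the second cell matches hypothesis b as written. The excess lies in the Discussion.
- **The Background does not make intact senses a necessary condition.** It says "When peripheral vestibular, visual, and somatosensory systems are intact", balance difficulty may be due to central weighting. A reader might take this to allow a central reading only when all three systems are intact. The text states no such restriction, and it also discusses reweighting in people with sensory impairment.
- **The Discussion does not claim proof.** It says that the result suggests impairment, and the end of the same sentence refers to subjects with normal vestibular function.
- **The sensory tests are not discarded.** They are named as potential covariates, and the title of Table 4 mentions classification. An article may leave the details to a fuller document. What remains is that the article states both a rule and a conclusion, and the conclusion outruns the rule.
- **A positive test need not mean abnormal CSMI.** Nothing in the protocol shows that failing the toe or ankle test moves the proprioceptive weight beyond 2 SD. The path is plausible on the protocol's own account, but its strength is not shown.
- **Net bias is not established.** This mechanism can only add people to the key cell. Others may remove them. Table 4 lists eight ocular motor and vestibular tests. If each used a 2 SD rule, any positive result counted, and the tests were independent and normal (all assumptions), 1 − (1 − 0.0455)^8 ≈ 31% of unaffected people would be flagged and leave the cell. A reader should not infer that the overall count is biased towards the hypothesis.

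**Conclusion.** The point holds in a limited form. The Discussion's phrase "even without peripheral sensory deficits" is not supported by the cell on which it rests, because that cell is silent on proprioception, and on the protocol's own account sensory abnormalities affect the CSMI weights. People with proprioceptive loss found at baseline could be counted towards the inference.

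The size is unknown. The range of 1.3 to 6.5 people rests on an assumed prevalence of 2% to 10% and is a ceiling for the key cell. The documents do not support the stronger reading that hypothesis b is tested wrongly, or that the key cell is filled mainly by people with sensory loss. Proprioception carries the point. Visual vertical adds little, since the protocol does not tie it to one peripheral system.

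**What to change.** 1. In the Study 1 Statistical analysis, keep the four cells as the answer to hypothesis b.
2. Add that the cell with abnormal CSMI and normal vestibular/ocular motor scores will be reported split by the Table 4 proprioception result. Show visual vertical for the same people descriptively, without using it to move anyone between cells.
3. In the Discussion, rest any statement that peripheral sensory deficits are absent on those with normal vestibular, ocular motor and proprioception results. Otherwise, narrow the statement to the scope of hypothesis b: "even without peripheral vestibular or ocular motor deficits". Either way, name ocular motor results in the condition as well as vestibular results, so that it matches the cell.

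The cost is small: one extra split and one reworded sentence, using a test already scheduled for the first visit. The subgroup behind the wider statement becomes somewhat smaller. A normal result on this simple position-sense test shows only that no deficit was detected, and the wording should say so.
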